**6.2.1 Inclusion Criteria**:

- 1. Residential/In-patients at recruitment to the study with a history of at least 2 weeks behavioural disturbance.
  2. Alzheimer’s Disease only as per NINCDS-ADRDA Criteria (McKhann et al 1984) + Haschinski Score<=4.

3.. Moderate to severe Alzheimer’s Disease (as determined by baseline MMSE < 19).

4. Clinically significant agitation that requires treatment.

5. Severity of agitation defined by Cohen Mansfield agitation inventory (CMAI) ≥ 45 (Cohen Mansfield 1995).

6. Age > 45.

- - 1. **Exclusion Criteria**

1.Memantine usage in the 4 weeks prior to the start of the study.

2. On Cholinesterase inhibitor for less than 3 months and not on a stable dose.

3. Anti-psychotic, antidepressant, benzodiazepine, lithium or hypnotic dosage alteration in the 2 weeks prior to the start of the study.

4. Antiparkinsonian medication.

5. Hypersensitivity to memantine or any of the excipients in the formulation.

6. Severe renal impairment.

7. Epilepsy or history of convulsions or receiving antiepileptic medication.

8. Concomitant usage of N-methyl-D-aspartate (NMDA) antagonists such as amantadine, ketamine or dextromethorphan.

9. Recent myocardial infarction, uncompensated congestive heart failure and uncontrolled hypertension.

10. Severe, unstable or poorly controlled acute or chronic medical illness.

11. Any disability that may interfere with the patient completing the study procedure.

12. Active malignancy.

13. Delirium pain or any medical illness as a clear cause of agitation.

14. Any important drug interactions: Prohibited during study and in the 14 days preceding enrolment/inclusion are: Analgesic dextromethorpan, Dopaminergics- amantadine. Warfarin in due to theoretical INR prolongation.

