During the study patients will be allowed to continue taking stable doses of concomitant medicines including antidepressants, antihypertensives, anti-inflammatory drugs, atypical anti-psychotics, anticoagulants, laxatives, diuretics, hypnotics and benzodiazepines (Tariot et al, 2004). Concomitant administration of anti-parkinsonian medication will be permitted but stable dose and no patients on amantadine this is to avoid difficulties with PD stability as Memantine can have benefit in PD. Cholinesterase inhibitors will not be permitted unless patients have been stable on that medication for at least 3 months. The commencement of new psychotropic medications will not be permitted during the study except for rescue treatment as per guidelines (appendix 6) for managing the behavioural symptoms of dementia.

- - 1. **Consent / Assent**

The patient or patient’s legally authorized representative must provides written informed consent (with the patients assent) to participate in the trial

- - 1. **Subject Identification**

Patients assessed for eligibility (*prior to consent / assent for participation in the trial*) will be assigned an **identification number.**

Once randomised into the trial (*post consent / assent for participation into the trial*) a subject will be assigned a **randomisation code.**

- - 1. **Stopping Rules** There are two criteria for removal of subjects from the trial;

1. Unblinding will occur in the event of life-threatening change in physical state or need for urgent medical and/or psychiatric intervention as requested by the patient’s treating physician in consultation with the study team and study monitoring committee.

2. Drop out from the 12 week-phase of the study is permitted due to intolerable side-effects and clinically significant persistent uncontrolled agitation. This will be a primary end point but will not necessitate un-blinding for that patient.

If patients withdraw their consent for follow-up then, if at all possible, the reason for loss to follow-up should be ascertained and permission should be requested to use data collected already for the purposes of the trial. No further data will be collected on patients who withdraw from follow-up. They have the right not to give a reason for withdrawing from follow-up and also to request that no data is held on them.

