Patients who have a history of previous failed treatment with memantine will not be entered. No medication changes should have occurred in the 7 days preceding trial commencement.

No other restrictions are placed on other prior or concomitant interventions. A list of all prior medications (& doses) will be obtained as part of baseline data collection.

- - 1. **Adverse Events**

Adverse Events will be managed by the Principal Investigator and Co-Director in line with the European Commission document ‘Detailed guidance on the collection, verification and presentation of adverse reaction reports arising from clinical trials on medicinal products for human use’ (Revision 1, 26th April 2004; Document ENTR/CT 3; <http://pharmacos.eudra.org/F2/pharmacos/new.htm>).

Serious Adverse Events are defined here as:

1. **Serious Adverse Events** – those which are fatal, life threatening, disabling or require hospitalisation or prolongation of hospitalisation. All deaths whether thought to be related to the trial intervention or not should be reported as serious adverse events.

1. **Unexpected Adverse Events** – those that would not be expected among elderly patients with AD (See known side effects in BNF).

If any patient suffers an event that fulfils these criteria, a Serious Adverse Event Form should be completed and faxed to the Principal Investigator **within 24 hours of the event being known.** The original form should be stored in the Investigator File and a copy placed in the patient’s source notes.

A trial (/annual) serious adverse events report will be compiled by the Principal Investigator and sent to the LREC. Serious Unexpected Adverse Events, in addition, will be reported immediately to the TSC .

Expedited reporting is required for all suspected adverse reactions that are both serious and unexpected. Fatal or life-threatening SUSARs should be reported to the LREC and the MHRA as soon as possible but no later than 7 calendar days after the sponsor has knowledge of the minimum criteria for expedited reporting. All other SUSARs and safety issues should be reported to the LREC and the MHRA as soon as possible but no later than 15 calendar days after the sponsor has first knowledge of the minimum criteria for expedited reporting.

Expedited reporting is not required for reactions which are serious but expected and for non-serious adverse reactions whether expected or not. Non-serious adverse events should be recorded using the Adverse Event Form.

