**Eligibility Assessment**

Name: DOB: Identification no.

Randomisation code: Date at baseline:

Investigator: Centre:

| **Inclusion checklist** | **Y or N** |
| --- | --- |
| Can consent/assent |  |
| Meets Mckann Criteria + Hachinski</=4 |  |
| CMAI>/= 39 |  |
| Agitation considered problematic. |  |
| Symptoms present for >2 weeks |  |
| In patient/Nursing home |  |
| MMSE</=19 |  |
| Age>/=45 |  |
|  |  |

| **Exclusion checklist** | **Y or N** |
| --- | --- |
| Memantine usage in prior 4 weeks |  |
| On Cholinesterase inhibitor for less than 3 months and dose not stable |  |
| Antispsychotic, anti-epileptic, antidepressant, benzodiazepine, lithium, or hypnotic dosage alteration in the 2 weeks prior to the start of study |  |
| Antiparkinsonian medication |  |
| Any contraindication to Memantine |  |
| Hypersensitivity to Memantine |  |
| Severe renal impairment |  |
| Epilepsy, history of convulsions or seizure, or epilepsy, or receiving any anti-epileptic treatment. |  |
| Concomitant usage of NMDA antagonists such as amantadine, ketamine or dextromethorphan |  |
| Concomitant use of Warfarin |  |
| Recent myocardial infarction, uncompensated congestive heart failure and uncontrolled hypertension |  |
| Severe, unstable or poorly controlled medical illness |  |
| Any disability that may interfere with the patient completing the study procedure |  |
| Active Malignancy |  |
| Delirium, pain or any medical illness as a clear cause of agitation. |  |
| Any important drug interactions: Prohibited during study and in the 14 days preceding enrollment/inclusion are: Analgesic dextromethorpan, Dopaminergics- amantadine , Warfarin due to theoretical INR prolongation. |  |

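### Antiparkinsonian medication is excluded outright in the criteria but permitted at a stable dose in the paragraph that follows; the warfarin and cholinesterase-inhibitor rules beside it are ambiguous.

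*Protocol*

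**What the plan says.** **Antiparkinsonian drugs.** Exclusion 4 in section 6.2.2 reads "4. Antiparkinsonian medication", with no exception. The synopsis has the same item, and the eligibility checklist in Appendix 1 lists "Antiparkinsonian medication" among the exclusions. The concomitant-medication paragraph directly after the exclusion list says "Concomitant administration of anti-parkinsonian medication will be permitted but stable dose and no patients on amantadine".

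**Warfarin.** Exclusion 14 prohibits certain drugs during the study and in the 14 days before enrolment, and ends with "Warfarin in due to theoretical INR prolongation". The checklist repeats this and also gives warfarin a line of its own. The concomitant-medication paragraph lists the medicines that may continue at stable doses, among them "atypical anti-psychotics, anticoagulants, laxatives, diuretics, hypnotics and benzodiazepines".

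**Cholinesterase inhibitors.** Exclusion 2 reads "On Cholinesterase inhibitor for less than 3 months and not on a stable dose". The synopsis and the checklist use the same *and* construction. The concomitant-medication paragraph says "Cholinesterase inhibitors will not be permitted unless patients have been stable on that medication for at least 3 months".

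Section 6.2 governs all of this: to enter, a patient must satisfy every inclusion criterion and no exclusion criterion.

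**The concern.** These passages decide who may be randomised. A screener who works from the criteria or the checklist turns away a patient on a stable antiparkinsonian drug other than amantadine. A screener who works from the concomitant-medication paragraph may accept the same patient. Screening is done by research fellows or CSOs at several trusts, and some sites were added by amendment, so different readings are foreseeable.

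Three things are at stake.

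- **Study population.** The ITT population in section 6.7.4 keeps every randomised and dosed patient with valid CMAI scores. Patients entered under either reading therefore stay in the primary analysis.
- **Eligibility deviations.** These cannot be judged consistently while two rules are in force.
- **Safety and co-treatment.** The warfarin prohibition carries a stated INR reason, and neither the baseline blood list nor the visit schedule includes a coagulation test that would bring a misreading to light. A recently started or changed cholinesterase inhibitor is a co-treatment that could affect behaviour within the 6-week CMAI window.

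**Working it through.** No figure in the protocol bears on this point and no arithmetic applies. The check sets the passages side by side.

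**1. Drug class against passage**

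| Drug class | Synopsis, 6.2.2 list and checklist | Concomitant-medication paragraph | Relation |
| --- | --- | --- | --- |
| Antiparkinsonian, not amantadine | Excluded | Permitted at a stable dose | Contradiction |
| Amantadine | Excluded | Not permitted | Agree |
| Warfarin | Prohibited by name | Its class may continue at stable doses; warfarin not mentioned | Ambiguous |
| Cholinesterase inhibitor | Excluded if short duration *and* unstable dose | Not permitted without 3 months of stability | Different logic |

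**2. Antiparkinsonian drugs.** Both statements are current text, and the amendment section does not mention either. Section 6.2 makes any single exclusion criterion decisive, so exclusion 4 and the permission cannot both be applied to a patient on a stable, non-amantadine drug.

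**3. Warfarin.** One text names a drug and the other names the class it belongs to. They can be reconciled by taking the class to mean anticoagulants other than warfarin, but the protocol does not say so. The very next sentence does make an explicit exception for amantadine, which makes the silence on warfarin easier to misread.

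**4. Cholinesterase inhibitors.** Let A be less than 3 months on the drug and B be a dose that is not stable. Exclusion 2 removes a patient when A and B both hold. The paragraph admits a patient only when neither holds, so it removes a patient when A or B holds. This takes stability to mean an unchanged dose.

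| Case | Exclusion 2 and checklist | Paragraph |
| --- | --- | --- |
| Under 3 months, dose not stable | Excluded | Excluded |
| Under 3 months, dose unchanged | Not excluded | Excluded |
| 3 months or more, recent dose change | Not excluded | Excluded |
| 3 months or more, dose stable | Not excluded | Allowed |

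The wordings differ in 2 of 4 cases. Exclusion 3, on recent dose changes, does not list cholinesterase inhibitors and so does not close the gap. Section 6.5.7 asks for no medication change in the 7 days before the trial starts. That narrows the two disputed cases to starts or changes earlier than that, but does not remove them.

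**The case against.** The strongest reply runs as follows, point by point.

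- **The criteria and checklist agree, and only one paragraph differs.** For antiparkinsonian drugs and warfarin this is true, and the form completed at screening gives one answer. It limits how often the conflict would take effect but does not remove it. Nor can the checklist simply be taken as the authority: it carries the looser cholinesterase wording, and its CMAI threshold is 39 where section 6.2.1 has 45.
- **The permission might concern use during the study, not entry.** This does not hold. A stable-dose condition, justified by the stability of Parkinson's disease, presupposes patients already on treatment.
- **Few patients are likely to be affected.** Inclusion 2 requires Alzheimer's disease only, and the Appendix 2 guidance says Parkinson's disease precludes even a possible diagnosis. The permission would then matter mainly for patients treated for another reason. This stands as a limit on size, and it is also a further sign that the permission does not fit the rest of the protocol.
- **Warfarin is a specific rule against general text.** This stands. A reader might infer a direct contradiction, but the documents support only a missing exception. Exclusion 14 also expressly covers the study period.
- **The two cholinesterase texts can be applied together.** This also stands. Exclusion 2 only excludes and permits nothing, so a reader who applies both ends with the narrower entry rule. What remains is that a screener using the checklist alone sees only the looser one.
- **Section 6.5.7 is no conflict.** A reader might take "No other restrictions are placed on other prior or concomitant interventions" as lifting the exclusions. It says only that nothing is added to restrictions stated already, and it repeals none of them.

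**Conclusion.** There is one true contradiction, on antiparkinsonian medication, and two lesser ambiguities, on warfarin and on the *and* in exclusion 2. The contradiction should be removed because it changes who may be randomised; the other two should be clarified in the same edit.

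The protocol gives no prevalence for any of these drugs, so the number of patients affected cannot be derived. A reader might infer that every screened patient on one of them gets opposite answers from different passages. That goes too far: amantadine users are barred by both texts, and so are patients both under 3 months and unstable on a cholinesterase inhibitor.

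A reader might also infer a biased treatment comparison. The documents do not support that. Allocation is randomised and blinded, so loose eligibility would be expected to affect both arms alike. The likely effects are an inconsistent study population and an unclear rule on a drug prohibited for a stated safety reason. Sample size and alpha are unaffected.

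The conclusion rests on the current wording alone and, for the cholinesterase cases, on reading stability as an unchanged dose.

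**What to change.** Reconcile the passages so that each of these drug classes has one rule, worded identically in the synopsis, the section 6.2.2 list, the concomitant-medication paragraph and the Appendix 1 checklist. In particular:

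- state in the concomitant-medication paragraph how antiparkinsonian drugs and warfarin are treated, so that it matches exclusions 4 and 14 as finally worded;
- make the and/or logic of exclusion 2, the checklist line and the narrative sentence on cholinesterase inhibitors agree.

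Which clinical rule applies to each class is for the investigators to decide. The cost is protocol wording and one checklist page, with no change to the sample size or the analysis.

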**Randomisation**

- - 1. **Recruitment Strategy**

We will employ a full time research doctor of post MRCPsych status. They will be involved in publicising the trial and maintaining awareness but the main role will be recruiting and following up patients. CSOs will be trained in assessing capacity with the purpose of consenting for participation in the trial, obtaining consent and undertaking the assessments. The screening will be supervised by a doctor who will also complete physical examination, review blood test results, complete Hachinski score, the diagnosis of probable dementia and the staging.

We will recruit from primary care and secondary care inpatients as well as direct from care homes. The research worker will assess the patient and meet with the family. We will recruit those patient who have a diagnosis of probable Alzheimers and clinically significant agitation as per inclusion criteria. The research doctor/CSO will liaise with primary care. There will also be site training on the rescue protocol and primary care will also be made available of the rescue protocol.

Eligible patients will be recruited from the Older Persons Mental Health inpatient Units at William Harvey Hospital Ashford and St Martins Hospital Canterbury—There are 116 beds in the trust. We will also have access to a further 184 beds from the West Kent trust if needed for recruitment. Our initial plan is to focus on 2 sites William Harvey and St Martins which have 90 beds in total. We will also recruit from 24 hour residential facilities in the region. We have good links already with care homes.

The Oxleas NHS trust site will recruit patients form inpatient wards (56 beds), nursing and residential homes where we have established partnerships with such institutions. There are around 2500 residential and nursing homes in the Oxleas district with some 300 + dementia nursing beds.  We will also be open to recruitment from community dwelling patients,
particularly those in receipt of the Oxleas home care for advanced dementia.

The Oxford site covers Oxfordshire, Berkshire, Buckinghamshire and South Northamptonshire. Recruitment will focus on the 3829 care home beds in Oxford and 3545 in Buckinghamshire (not including Milton Keynes). Patients will also be identified through the Deeparc System.

Peterborough and Plymouth site will use similar recruitment.

As well as contacting teams for referrals we will also actively identify patients in residential homes with significant levels of agitation in need for treatment. These patients will need to be under the care of local CMHTs. Alongside with these methods, patients will be identified from within the Dementia Electronic Prescribing & Research Contact (DEEPARC) database, by the administrator of this system. This system is managed by the Dementia & Neurodegenerative Diseases Research Network (DeNDRoN). This is a Countywide electronic register of people with dementia, for prescribing purposes. It also holds a register of patients who have given their consent to be contacted about research studies, for which they may meet the eligibility criteria. Where a person has agreed to be contacted about research, the research nurse or DEEPARC administrator, will first check with the treating clinician that it would be appropriate for the research team to contact the patient and caregiver.

Clinically significant Agitation is reported to occur in at least 30-40% of patients with dementia across the settings proposed (Boustani et al 2005; Gruber-Baldini et al 2004; Steffens et al 2005)- Average length of inpatient stay was 16 weeks for the proposed recruitment sites. Any patients discharged before the end of the trial will be followed up for the trial duration and will work with local team follow up. Patients in residential placements will be on long term placement. If patients in residential care are unknown to the local community mental health team and it is indicated then referral will be facilitated.

We anticipate being able to recruit at least 6-8 patients per month for the 21 month length of recruitment. The target recruitment is 164 assuming 20% drop out rate (Section 6.7).

- - 1. **Contact with potential sources of referrals.**

All of the consultants in the region will be contacted by telephone and letter and informed of the study at the outset. General practitioners who provide care to residential homes in Shepway and Oxleas will also be contacted. There will also be communication with ward nurses. As it is anticipated consultants will be one of the main sources of referral, personal contact will be made whenever possible. One of the liaison nurses will be directly involved in the trial to assist in recruitment which will be primarily the responsibility of the research fellow.

All old age psychiatrists in the area will be contacted. This will be done by introductory letter. They will be informed of the study design and objectives, and also of inclusion/exclusion criteria. The patients clinician will be requested to ask permission of the patient with dementia and/or carer for the research fellow/CSO to approach the patient.

In addition contact will be made with local branches of Alzheimers Disease society in the region, to inform their members about the trial.

As long as the above has occurred every newly admitted patient be approached within 48 hours to determine eligibility criteria then carer contacted via a phone/face-to-face and obtained written consent. In addition, all patients who are already being in the unit for more than 48 hours to be screened then contact their carer if they met eligibility criteria.

- - 1. **Lists of potential subjects**

Basic details on all potential patients will be obtained from referrers. The following information will be sought.

1. Name
2. Date of Birth
3. Gender
4. Ethnicity
5. Address
6. Details of physician treating Alzheimer’s disease
7. GP details
8. Carer/Relative Name, Address and Telephone Number
9. Relationship of Relative to patient

It is expected that i) to ix) will be obtained for all patients assessed for eligibility for the trial. The Trial Research Fellow/CSO will confirm that the details are correct once written informed consent or assent has been obtained.

- - 1. **Screening for Eligibility**

Screening for eligibility will take place prior to baseline assessment. It will be performed by the research fellow/CSO in the trial.

- - 1. **Patient Information**

Once preliminary eligibility has been determined, the research fellow /CSO will approach patients and their carers individually to discuss the possibility of their entering the trial. All eligible patients will be given a copy of the Patient Information Sheet and given an opportunity to discuss any queries they may have about the trial at this stage.

- - 1. **Capacity Assessment & Relative Information**

Capacity is the ability somebody has to consent to participate in the study. This is based on their ability to understand what the study involves, to remember what you have told them, and to reach a decision based on a weighing up of the risks and benefits involved. Lack of capacity is an inability to do these things.

Relevant recent studies in the speciality used the following:

Tariot et al (2004) – written informed consent was obtained from the caregiver and either the patient (if possible) or a legally acceptable representative (if different from the caregiver) prior to initiation of the study.

Ballard et al (2005) – all participants or next of kin or other appropriate representative if required gave informed consent.

For the purposes of this trial, the research fellow/CSO will assess Capacity for each patient on an informal basis during the eligibility assessment. Patients will be deemed to have the capacity to decide to enter the trial if they can understand the implications of the trial for them and are able to communicate a decision. They will need to know that they are entering into a trial that will involve them being assessed by the trial team, require them to have blood tests and receive either active or placebo medication.

Where somebody is deemed to lack Capacity they will not be excluded from taking part in the trial. A judgement should be made as to whether the patients would be willing to participate were they able to consent themselves. This judgement will involve the carer, relative, advocate or guardian as appropriate. We will rely on them to use their previous knowledge of the patient in terms of any stated preference for research, whether they would agree to take part in research if they had capacity.. Patients also need to demonstrate cooperation with participating in the trial for example undergo interview and take medication. If it is felt that the patient would not be willing to participate or cooperate in the trial they will be excluded. Careful consideration will be given to any distress that the patient with dementia may experience as a result of interviews and recruitment. This is an approach which has been used successfully in trials and other descriptive and evaluative studies.

Carers of patients with and without capacity (with the agreement of the patient) will be sent / given a copy of the Information Sheet (see appendix 1). Up to one week later (but no less than 24 hours later) the research fellow/CSO will contact the carer to answer any queries they may have about the trial and to ask them if they are happy to proceed.

- - 1. If the carer is unhappy to proceed the patient will be excluded from the trial.
    2. If the carer is happy to proceed an appointment will be made between the research fellow/CSO and the carer to obtain written informed assent.
    3. **Consent and Assent**

Written informed consent should be obtained for all eligible patients with capacity.

Written informed assent should be obtained for all eligible patients without capacity from the patient’s carer.

- - 1. **Baseline Assessments**

Baseline assessments relate to all research data collected prior to randomisation. **No protocol activity involving contact with the patients should take place before written informed consent or assent is obtained.**

Baseline data collection will be carried out at one time point whenever possible. To maximise efficiency all data will be collected during one visit. The following data will be collected;

1. Medical history
2. Functional Assessment Staging (Reisberg et al 1988)
3. Cohen Mansfield Agitation Inventory (Cohen Mansfield 1995b)
4. Neuropsychiatric Inventory (Cummings et al 1994)
5. MMSE (Folstein et al 1975)
6. Clinical Global Impression of Change scale (Guy 1976) severity at baseline and change thereafter
7. Severe Impairment Battery (Saxton et al 1990)
8. Standard side effect scale
9. Hachinksi Ischaemia index
10. List of Current Medications & Dose
11. Quality of Life in Alzheimer’s Disease Scale (QolAD) (Logsdon et al 2000)

All scales are provided at appendix 2 + 3 + 4

The research doctor or the CSO under the supervision of the PI will assess the patient, examine the medical notes/ care plans, talk to the key nurse on the ward/assisted living placement and the patients relative if possible to assist with the rating tools.

1. The researcher/CSO will ensure that the caregiver providing information has had at least 4 hours contact over the week with the patient and if possible will repeat with the same caregiver or staff with the same knowledge of the patient at later rating points.

In addition to the above, the following investigations will be performed. If recent results are available (within the last month) these will be used instead of repeating the investigation.

1. Physical examination
2. Weight
3. Blood pressure
4. ECG if clinically indicated

iv Temperature

v. blood tests: FBC, UEs, LFTs, TFTs, Glucose,B12, Folate, Cholesterol

- 1. **Randomisation & Enrolment**
     1. **Flowchart**

Consented patient with baseline assessment performed.

Allocation derived from randomisation

Treatment code allocated to patient

Treatment code corresponds to pre-randomised medication

Memantine arm

Placebo arm

- - 1. Method of Assigning Patients To Trial Arms

Patients will be allocated to one of the two trial arms (ratio 1:1). Once informed consent or assent has been given, baseline assessment completed , the research fellow/CSO will obtain a treatment code for the subject. Patients will be assigned codes consecutively as they enter the trial. The codes will correspond to the pre-randomised medication packs provided by Lundbeck. There will be a sealed envelope for each treatment code containing details of whether the medication pack for that code contains active drug or placebo. Balancing for severity of agitation, staging of dementia and smoking status will be included. Randomisation using the minimisation approach will ensure that equal numbers are entered into each arm of the trial. Patients will be registered for the trial using an internet allocation system.

- - 1. **Blinding & Unblinding**

It is important that blinding is maintained throughout the trial until the database is closed and the data analyses have been performed.

Unblinding will occur in the event of life-threatening change in physical state or need for urgent medical and/or psychiatric intervention as requested by the patient’s treating physician in consultation with the study team and study monitoring committee.

Unblinding in such circumstances will only occur if it is felt that knowledge of the patients medication status will impact on future medical care.

If unblinding occurs accidentally, it is important that the unblinded individual completes an Accidental Codebreak Form (see Appendix4) for each instance of unblinding (copies will be available from the Trial Research Fellow/CSO).

- 1. **Trial Interventions**
     1. **Flowchart**

